## Aims

The current study builds upon the feasibility study by examining the effect of a multi-component voucher based intervention on the cardiovascular fitness and MVPA levels of teenagers aged 13–14 years in seven schools in Swansea (4 intervention and 3 control schools). The specific aims of the ACTIVE Project are as follows:

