## Analysis

CONSORT guidelines will inform the analysis and presentation of the study [47]. Multilevel regression analyses will test the effect of the intervention on our primary and secondary outcome measures in comparison with the control arm. We will adjust for baseline, 6 month, 12 month and 18 month follow-up scores and baseline characteristics (e.g. sex). Focus groups will be analysed via thematic analysis in order to identify key themes from discussions with pupils involved in the project [48]. Quantitative measures will be linked to the SAIL databank to analyse the impact of physical activity levels on educational attainment and GP visits. COREQ (Consolidated Criteria for Reporting Qualitative Research) will be followed for the qualitative aspects of the research.

This RCT will examine change in the intervention group compared to controls. Findings from the feasibility study showed that sedentary behaviour reduced by 65 min (95% CI: 12.0 to 117.6) from baseline (*n* = 75). A previous study [49] had an intracluster correlation of fitness scores across 10 schools of 0.16. Therefore, estimating a reduction in sedentary behaviour of 65 min (intervention) and 15 min (control) with a standard deviation of 30 min, and an average cluster size of 150 children per school ICC of 0.16, coefficient of variation of cluster sizes of 0.9, power of 80% and significance of 5% would require 450 children per arm in 3 schools in each arm (6–8 schools in total depending on consent rates).

Fitness improved in the feasibility study in the intervention group by 98 m (95% CI: 19 to 177, children ran 1730 m in 12 min at baseline and 1823.3 m at post intervention). Therefore, estimating improvement in cooper run of 98 m (intervention) and 22 m (control) with average cluster size of 150 children per school and ICC of 0.16 (as above) would require 300 children or 2 schools per cluster (3 schools if consent rate is assumed to be 60%).

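### The Cooper run sample size of 300 children or 2 schools per arm needs an SD of about 67 m or less, which the feasibility confidence interval in the same paragraph does not support

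*Protocol article*

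**What the plan says.** The protocol article makes the Cooper run test the primary aim (Primary aims). Its sample size is justified in the last paragraph of Analysis. The target is given as "estimating improvement in cooper run of 98 m (intervention) and 22 m (control"), a difference of 76 m, and the stated requirement is "with average cluster size of 150 children per school and ICC of 0.16 (as above) would require 300 children or 2 schools per cluster", or three schools at 60% consent.

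No SD is given for the run. The only SD in the section belongs to sedentary time ("with a standard deviation of 30 min"). The other settings also appear only in the sedentary-time paragraph: "coefficient of variation of cluster sizes of 0.9, power of 80% and significance of 5" per cent.

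The paragraph on the run does report the feasibility result: "Fitness improved in the feasibility study in the intervention group by 98 m (95% CI: 19 to 177"). It prints no number of children for it; the n of 75 stands beside the sedentary-time result. The Feasibility study section gives 115 pupils in all.

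The trial itself is to run "in seven schools in Swansea (4 intervention and 3 control schools") (Aims).

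**The concern.** A condensed article may leave an SD to the full protocol, so its absence alone is no error. But the printed difference, cluster size, ICC and sample size fix the largest SD at which 80% power is reached, and that value can be compared with the feasibility interval in the same paragraph. The two are several-fold apart.

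This is the only sample-size justification for the primary aim. It tells readers that two or three schools per arm are enough for a 76 m difference. If that is wrong, a non-significant primary result could be read as evidence against the intervention when the trial had little chance of detecting its own target.

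**Working it through.** **Inputs.** From Analysis: difference 98 − 22 = 76 m; 150 children per school; ICC 0.16; feasibility interval 19 to 177 m. Carried over from the sedentary-time paragraph: 80% power, 5% significance (two-sided assumed), CV 0.9. From Aims: 4 v 3 schools.

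**Design effect.**
- Equal clusters: 1 + 149 × 0.16 = 24.84.
- With CV 0.9: 1 + ((1 + 0.81) × 150 − 1) × 0.16 = 44.28.

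**Can the stated figure be reproduced?** Not directly, because the SD is missing. Without clustering, n per arm = 2 × (1.96 + 0.84)² × (SD/difference)² = 15.70 × (SD/difference)². Two routes lead to the stated figure:
- For sedentary time, 15.70 × (30/50)² = 5.65; × 44.28 = 250 children, or 2 schools; one added school makes 3, or 450 children, as stated. If 30 is carried over to the run as metres, 15.70 × (30/76)² = 2.45; × 44.28 = 108 children, or 1 school; one added makes 2, or 300 children.
- With clustering ignored, 300 per arm corresponds to an SD of about 332 m.

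Both are conjecture; the article does not say which, if either, was used.

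**SD that the stated size requires.**
- Equal clusters: 300/24.84 = 12.08 effective children; SD = 76 × √(12.08/15.70) = 66.7 m.
- With CV 0.9: 300/44.28 = 6.78; SD = 76 × √(6.78/15.70) = 49.9 m.

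These use the normal approximation, which flatters a comparison of two schools with two.

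**SD that the feasibility interval implies.** SE = (177 − 19)/3.92 = 40.3 m.
- Paired change, SD = SE × √n: 221 m at n = 30, 349 m at n = 75, 432 m at n = 115.
- Unpaired, n at each time, SD = SE × √(n/2): 156 m at n = 30, 247 m at n = 75. These are cross-sectional SDs, before baseline adjustment.
- An SD of 66.7 m would need n = (66.7/40.3)² = 2.7, about 3 children.

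Baseline adjustment can lower these. From a paired SD, the residual SD is SD × √((1 + r)/2), so 349 m becomes 247 to 349 m for r from 0 to 1. From the unpaired 247 m, an assumed correlation of 0.7 gives 247 × √(1 − 0.49) = 176 m.

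**Power of the 4 v 3 schools for 76 m.** SE = SD × √(DE/150 × (1/4 + 1/3)), with a two-sided t-test on 5 df. Example: SD 349 m, DE 24.84 gives SE 108.5 m, noncentrality 76/108.5 = 0.70, power 8.9%. At ICC 0.02 the design effects are 1 + 149 × 0.02 = 3.98 and, with CV 0.9, 1 + (271.5 − 1) × 0.02 = 6.41. The detectable difference at 80% power is 3.51 × SE; the last two columns use equal clusters.

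| SD (m) | Power, ICC 0.16 | Power, ICC 0.16, CV 0.9 | Power, ICC 0.02 | Power, ICC 0.02, CV 0.9 | Detectable, ICC 0.16 | Detectable, ICC 0.02 |
|---|---|---|---|---|---|---|
| 156 | 24.8% | 16.1% | 87.5% | 69.6% | 170 m | 68 m |
| 176 | 20.6% | 13.7% | 79.1% | 59.5% | 192 m | 77 m |
| 221 | 14.8% | 10.5% | 60.4% | 42.2% | 241 m | 97 m |
| 247 | 12.8% | 9.4% | 51.4% | 35.3% | 270 m | 108 m |
| 349 | 8.9% | 7.2% | 29.6% | 20.3% | 381 m | 153 m |
| 432 | 7.5% | 6.4% | 21.1% | 15.0% | 472 m | 189 m |

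**Schools needed at SD 349 m, ICC 0.16.** 15.70 × (349/76)² = 331 children; × 24.84/150 = 54.8, so 55 schools per arm (98 with CV 0.9), against the stated 2.

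**The case against.** The strongest reply is that the feasibility SD is not known. The n of 75 is printed for sedentary time, not the run, and a paired analysis is an assumption. The printed means differ by 1823.3 − 1730 = 93.3 m, not 98 m, so the estimate may come from different subsets of children or from a model. A reader might infer that the interval fixes the SD near 350 m and the trial's power near 10%; the documents do not support that precision. This stands, and it is why a range is given. It does not rescue the stated size, because no plausible n brings the SD near 67 m.

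The second reply concerns the ICC. The value of 0.16 comes from fitness scores in another study, and the ICC after baseline adjustment could be much lower. This also stands: at an assumed 0.02, power is 30% at SD 349 m, 60% at 221 m and 79% at 176 m, and it passes 80% at 156 m, all with equal clusters. So one cannot say that the trial could not detect 76 m under any assumptions. But the plan uses 0.16 for this calculation.

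A reader might also note that three schools at 60% consent give 3 × 90 = 270 children, fewer than 300. That is no fault. Three schools of 90 carry 270/15.24 = 17.7 effective children, against 12.1 for two schools of 150. The printed wording that puts the requirement per cluster is only a slip for per arm. That the CV is not repeated for the run is no separate error, since the back-reference to the previous paragraph may cover it.

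**Conclusion.** The point holds. The stated primary-outcome size is incompatible with the feasibility interval beside it: it needs an SD of at most about 67 m (50 m with CV 0.9), while the interval gives 221 to 432 m for a paired change with n from 30 to 115, or about 247 m unpaired with 75 at each time. At the plan's ICC of 0.16, the 4 v 3 schools have far less than 80% power for 76 m: about 9% at SD 349 m, and about 6 to 25% over SDs from 432 down to 156 m, with and without the CV.

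This rests on carrying over 80% power and two-sided 5% significance, on 150 children per school, and on a t-test with 5 df. The size of the shortfall depends on the unprinted feasibility n, the type of comparison and the ICC. That there is a large shortfall at ICC 0.16 does not. The error should be corrected before the paragraph is relied on as the power statement for the primary aim.

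**What to change.** Rewrite the last paragraph of Analysis:
- State the Cooper run SD used, its source and the number of feasibility children behind it, and whether it refers to raw scores, change or a baseline-adjusted residual.
- Apply the design effect including the CV of 0.9.
- Replace the requirement of 300 children or 2 schools with the power and minimum detectable difference of the 4 v 3 schools, over a stated range of SD and ICC and allowing for the small number of clusters.
- Remove the implication that the design is adequately powered for 76 m.
- Correct the slip to per arm.

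The cost is one paragraph and a stated power that is much less favourable. The correction itself needs no additional schools.

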## Conclusion

ACTIVE is a novel intervention aimed at examining the effect of a multi-component intervention in improving the cardiovascular fitness, arterial physiology and general health, whilst reducing time spent sedentary, in adolescents. Providing insight into the results of the trial, alongside process evaluation can strongly add to the evidence base in this field and can inform future intervention and policy involving teenagers and physical activity.

## Appendix 1

**INTERVENTION FOCUS GROUP TOPIC GUIDE – PARTICIPANTS – PRE-INTERVENTION.**

*Activity 1 (5–10 min):* What is physical activity? What does it mean to you?

*(Ask pupils to discuss/write down what the term means to them).*

How active should people your age be? (60 min recommended per day).

*Question 1:* How active do you think people in your year are? Do you think you are as active as you can be?

*Activity 2 (5–10 min):* What do you see as the current barriers to physical activity? How do you feel about your current levels?

*(Give post-it notes and ask pupils to list 5–6 barriers to activity. Then rank these barriers in order of most common barriers and discuss the reasoning for this order).*

*Question 2:* Why do you think people your age like/don’t like being active? Is there much to do in your area? If so, how accessible are these activities to your age group?

*Question 3:* Vouchers are currently accepted by *(refer to list of participants).* What other activities or providers would you like to see included before we start?

*Question 4:* Having heard the way the scheme is set up; do you think there will be any problems? What do you think we could do about these problems? Do you think we should do things differently?

*Question 5:* What is the best way of letting everyone in the school know about this scheme? When are the best times for the support worker to be available in the school?

*Question 6:* Do you have anything else to add about the project?

**CONTROL FOCUS GROUP TOPIC GUIDE – PARTICIPANTS – PRE-INTERVENTION.**

*Activity 1 (5–10 min):* What is physical activity? What does it mean to you?

*(Flipchart/post-its – ask pupils to discuss/write down what the term means to them).*

How active should people your age be? (60 min recommended per day).

*Question 1:* How active do you think people in your year are? Do you think you are as active as you can be?

*Activity 2 (5–10 min):* What do you see as the current barriers to physical activity? How do you feel about your current levels?

*(Give post-it notes and ask pupils to list 5–6 barriers to activity. Then rank these barriers in order of most common barriers and discuss the reasoning for this order).*

*Question 2:* Why do you think people your age like/don’t like being active?

*Question 3:* Is there much to do in your area? If so, how accessible are these activities to your age group?

*Question 4:* Are your friends/family active? Does this influence you?

*Question 5:* What is the best way to get people your age active?

*Question 6:* Do you have anything else to add?
